## Abstract

**Background:**

It is well established in studies across several countries that tobacco smoking is more prevalent among schizophrenic patients than the general population. Electronic cigarettes are becoming increasingly popular with smokers worldwide. To date there are no large randomized trials of electronic cigarettes in schizophrenic smokers. A well-designed trial is needed to compare efficacy and safety of these products in this special population.

**Methods/Design:**

Intervention: We have designed a randomized controlled trial investigating the efficacy and safety of electronic cigarette. The trial will take the form of a prospective 12-month randomized clinical study to evaluate smoking reduction, smoking abstinence and adverse events in schizophrenic smokers not intending to quit. We will also monitor quality of life, neurocognitive functioning and measure participants’ perception and satisfaction of the product.

Outcome measures: A ≥50% reduction in the number of cigarettes/day from baseline, will be calculated at each study visit (“reducers”). Abstinence from smoking will be calculated at each study visit (“quitters”). Smokers who leave the study protocol before its completion and will carry out the Early Termination Visit or who will not satisfy the criteria of “reducers” and “quitters” will be defined “non responders”.

Statistical analysis: The differences of continuous variables between the three groups will be evaluated with the Kruskal-Wallis Test, followed by the Dunn multiple comparison test. The differences between the three groups for normally distributed data will be evaluated with ANOVA test one way, followed by the Newman-Keuls multiple comparison test. The normality of the distribution will be evaluated with the Kolmogorov-Smirnov test. Any correlations between the variables under evaluation will be assessed by Spearman r correlation. To compare qualitative data will be used the Chi-square test.

**Discussion:**

The main strengths of the SCARIS study are the following: it’s the first large RCT on schizophrenic patient, involving in and outpatient, evaluating the effect of a three-arm study design, and a long term of follow-up (52-weeks).

The goal is to propose an effective intervention to reduce the risk of tobacco smoking, as a complementary tool to treat tobacco addiction in schizophrenia.

**Trial registration:**

ClinicalTrials.gov, NCT01979796.

## Background

It is well established in studies across several countries that tobacco smoking is more prevalent among schizophrenic patients than the general population [1]. For example, in the US, 80% or more of schizophrenic patients smoke, compared to approximately 20% of the general population [2]. An increased rate of smoking among subjects with schizophrenia contributes to multiple negative health effects, including higher rates of coronary heart disease, hypertension, respiratory disease and lung cancer than in the general population [3]. Randomized clinical trials of currently marketed smoking cessation products (varenicline, bupropion, nicotine replacement therapy) in schizophrenia have shown limited effects [4]. This scenario is further complicated by the belief that quitting smoking will worsen psychiatric symptoms, or that these patients have little or no interest in quitting. Moreover, the prescribing information for bupropion and varenicline, two important first-line medications for nicotine dependence, carry a *black-box* warning highlighting an increased risk of psychiatric symptoms and suicidal ideation in patients reporting any history of psychiatric illness [5].

Electronic cigarettes (e-cigarettes) are becoming increasingly popular with smokers worldwide. Users report buying them to help quit smoking, to reduce cigarette consumption, to relieve tobacco withdrawal symptoms, and to continue having a smoking experience, but with reduced health risks [6]. A recent randomized controlled trial (RCT), showed that smokers not immediately willing to quit who used e-cigarettes substantially decreased daily cigarette consumption without significant side effects [7]. In a prospective 12-month pilot study, e-cigarettes were shown to substantially decrease cigarette consumption without causing significant side effects in schizophrenic smokers not intending to quit [8], however, in a recent large randomized clinical trial of e-cigarettes conducted in 300 smokers, side effects that are commonly recorded during smoking cessation trials using drugs for nicotine dependence were infrequently reported during the course of the study [7]; for example, at week-2, hunger, insomnia, irritability, anxiety, and depression were reported by 6.5%, 4.0%, 3.5%, 3.0% and 2.0% of participants, respectively. Moreover, no serious adverse events (AEs) (that is, major depression, abnormal behavior or any event requiring an unscheduled visit to the family practitioner or hospitalization) occurred during the study. Quitters also reported improved quality of life, which could be used to motivate attempts to quit by individuals with concerns about what life will be like without cigarettes [9] Some authors suggest the hypothesis that smoking causes cognitive decline and loss of gray-matter tissue in the brain over time [10].

### Research plan

To date there are no large randomized trials of e-cigarettes in schizophrenic smokers. A well-designed trial is needed to compare efficacy and safety of these products in this special population.

### Objectives

#### Primary

The primary outcome is the evaluation of the efficacy and safety of a popular electronic cigarette brand. The trial will take the form of a prospective 12-month randomized clinical study to evaluate smoking reduction, smoking abstinence and AEs in schizophrenic smokers not intending to quit, experimenting with two different nicotine strengths of e-cigarette.

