#### Secondary outcomes

The secondary outcomes are to monitor AEs, quality of life, neurocognitive functioning, and spirometry, and to measure participants’ perception of and satisfaction with the product.

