### Study outcome measures

A reduction ≥50% in the number of cigarettes/day from BL, defined as self-reported reduction in the number of cigarettes/day (≥50%) compared to BL (together with an eCO levels reduction, to objectively document a reduction from baseline), will be calculated at each study visit (referred to as reducers). Abstinence from smoking, defined as complete self-reported abstinence from tobacco smoking - not even a puff (together with an eCO concentration ≤7 ppm), will be calculated at each study visit (referred to as quitters). Smokers who do not satisfy the criteria of reducers or quitters will be defined non responders. Smokers who leave the study protocol before its completion due to lack of efficacy or poor tolerability of the product under investigation, will carry out the early termination visit and will be defined as non responders.

AEs, symptoms thought to be related to tobacco smoking and e-cigarette use, and to withdrawal from nicotine, will be annotated at BL and at each subsequent study visit on the AE page of the study diary. Vital signs will be also recorded. The number and the percentage of subjects experiencing AEs, adverse reactions, serious AEs and AEs leading to study withdrawal will be summarized by treatment group. AEs will also be summarized by system organ class and preferred term using the *MedDRA* dictionary.

Quality of life, neurocognitive functioning and psychopathological status will be reassessed by QLS, BACS and PANSS, respectively. Participants’ perceptions and liking of the product will be assessed by asking them to rate their levels of satisfaction with the products compared to their own cigarettes using a VAS, scoring from 0 to 10 points (0 = completely unsatisfied, 10 = fully satisfied). Using the same scale, they will also rate how much they miss their own brand (0 = did not miss it at all, 10 = missed it too much) and whether they would recommend it to a friend/relative (0 = not recommended at all, 10 = absolutely recommended).

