### Sample size

All statistical tests were two-tailed and were considered to be statistically significant at *P* < 0.05. A sample size of 133 subjects was calculated accepting the following parameters: effect size medium = 0.30; alpha = 0.05; 1-ß = 0.80. Considering a drop-out rate of 15%, a total sample size of 153 smokers was determined. The smokers will be randomized into the three arms of our study protocol (51 smokers for each arm).

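### No single variable or visit is named as primary, so the protocol does not exclude claiming efficacy from whichever endpoint, visit or arm pair crosses 0.05

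*Protocol article*

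**What the plan says.** All references are to the protocol article.

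- **Objectives, Primary.** "The primary outcome is the evaluation of the efficacy and safety of a popular electronic cigarette brand". The next sentence describes a 12-month randomized study "to evaluate smoking reduction, smoking abstinence and AEs in schizophrenic smokers not intending to quit". The three components are not ranked.
- **Objectives, Secondary outcomes.** "The secondary outcomes are to monitor AEs, quality of life, neurocognitive functioning, and spirometry". AEs therefore sit in both tiers.
- **Study outcome measures.** A reduction of at least 50% in cigarettes per day, with a fall in exhaled carbon monoxide (eCO), "will be calculated at each study visit (referred to as reducers"). Complete abstinence with eCO of 7 ppm or less "will be calculated at each study visit (referred to as quitters"). AEs "will be annotated at BL and at each subsequent study visit on the AE page of the study diary". Of their analysis the section says that counts and percentages, down to "AEs leading to study withdrawal will be summarized by treatment group"; it names no test.
- **Study design.** There are three arms and five follow-up visits, at weeks 4, 8, 12, 24 and 52.
- **Sample size.** "All statistical tests were two-tailed and were considered to be statistically significant at" P < 0.05. The calculation uses a medium effect size of 0.30, alpha 0.05 and power 0.80, and gives 133. It does not say which outcome, test or visit these refer to.
- **Statistical methods.** Dunn and Newman-Keuls comparisons follow the three-group tests of continuous variables. Qualitative data get chi-square with Yates correction or Fisher's exact test, with no procedure for several comparisons.

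**The concern.** The two efficacy measures in the primary objective are categorical. They are evaluated at several visits and can be compared across three arms or in three pairs. A nominal 5% error rate and a stated power have meaning only for an identified test, and the text identifies none.

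The cues on timing also point in different directions. The objective speaks of 12 months, the product is supplied for 12 weeks, and Study design describes a further efficacy and safety evaluation at 24 weeks.

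At stake is the main conclusion. With nothing fixed in advance, a significant result on one measure, at one visit, for one pair could be presented as the trial's efficacy finding. A reader could not tell whether it was the planned test or the most favorable of many.

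**Working it through.** **1. The plan's own figure.** For a chi-square test with effect size w, the noncentrality is N × w². Power is the probability that a noncentral chi-square exceeds the 95th percentile of the central one. With w = 0.30 and N = 133, noncentrality is 133 × 0.09 = 11.97. The smallest N giving power 0.80 depends on the degrees of freedom (df):

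| df | N for power 0.80 | Power at N = 133 |
|---|---|---|
| 1 | 88 | 0.93 |
| 2 | 108 | 0.88 |
| 3 | 122 | 0.84 |
| 4 | 133 | 0.801 |
| 5 | 143 | 0.77 |

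Only df = 4 returns 133. Other readings of 0.30 do not: one-way ANOVA with f = 0.30 gives 111 in total, two means with d = 0.30 gives 175 per arm, and a correlation of 0.30 gives about 85. A table of 3 arms by 3 categories has (3 − 1) × (3 − 1) = 4 df. So 133 fits one test of quitter / reducer / non responder across the arms, done once at 0.05.

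**2. The number of efficacy tests the text leaves open.** Two endpoints × 5 visits = 10 three-arm tests. With 3 pairs each, 10 × 3 = 30 pairwise tests. AEs are left out because the plan only summarizes them.

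**3. Reference value if tests were independent.** 1 − 0.95^10 = 0.40 for 10 tests. For one endpoint at five visits it is 1 − 0.95^5 = 0.23, and for two endpoints at one visit 1 − 0.95^2 = 0.0975. Repeated measures on the same people are positively correlated, so these overstate the risk.

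**4. Allowing for correlation.** The documents give neither event rates nor correlations. The assumptions are 51 per arm, no difference between arms, 30% with at least 50% reduction (including 10% quitters), and within-person latent correlation of 0.5, 0.7 or 0.9. Chance of at least one P < 0.05:

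| Family | 0.5 | 0.7 | 0.9 |
|---|---|---|---|
| 10 three-arm tests, simulated participants | 0.35 | 0.31 | 0.26 |
| 10 three-arm tests, second model | 0.29 | 0.22 | 0.13 |
| 30 pairwise tests, Yates | 0.40 | 0.37 | 0.30 |
| 30 pairwise tests, no correction | 0.64 | 0.59 | 0.50 |

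The second model draws correlated 2-df statistics directly and needs no event rates. One three-arm test at one visit gives 0.05.

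**5. Pairs at a single visit.** Three uncorrected pairwise tests of one endpoint give about 0.12. With the Yates correction named in Statistical methods, this falls to about 0.07 to 0.08 for reduction and about 0.05 for abstinence. Most of the inflation under the named test therefore comes from multiple visits and endpoints, not from arm pairs.

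**The case against.** The strongest reply has four parts.

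*An article condenses a fuller protocol, and alpha hierarchies are usually left to the analysis plan.* This stands in part: the lack of a detailed multiplicity scheme is not in itself a fault here. But the article has a section headed Primary, a section defining outcomes and a general significance rule. It fills all three without identifying a primary variable or visit, and it places AEs in two tiers. That is on the page.

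*The significance level is a threshold, not a rule for success, and calculating status at each visit is not the same as testing it there.* This stands. A reader might infer that the protocol declares the trial positive if any test crosses 0.05; it says no such thing. It merely does not exclude that use, and the families of 10 and 30 tests are what it leaves open, not tests it lists.

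*AEs are summarized, not tested.* This stands. A reader might count AEs as a third primary outcome tested at 0.05, but no AE test is named, so none enters the figures.

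*The larger error rates do not use the planned test.* This also stands. The 50 to 64% for pairs, and 12% for pairs at one visit, apply to uncorrected chi-square, which only the abstract suggests.

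**Conclusion.** The concern holds for the efficacy outcomes: the protocol fixes no primary variable and no primary visit, and the duplicate listing of AEs is a plain inconsistency. If the open comparisons were all read at 0.05, the chance of a false positive would be about 26 to 35% for 10 three-arm tests (13 to 29% in the second model) and about 30 to 40% for 30 Yates-corrected pairwise tests. These figures depend on the assumed rates and correlations, but every multi-visit result is well above 5%.

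Three further inferences go beyond the text.

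- The 133 was not stated to come from a 3 × 3 table. The match at df = 4 suggests that one response-category test was intended, but no test or table is named.
- Quitters usually meet the reducer definition too, but not by necessity. A reducer needs a fall in eCO from baseline, a quitter needs 7 ppm or less, and the inclusion criteria set no minimum baseline eCO.
- Week 52 is not dictated as the primary visit. It fits the 12-month objective, but the text equally permits week 12.

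**What to change.** Before enrollment, amend the protocol as follows.

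1. Name one primary endpoint: response in three mutually exclusive categories (quitter; reducer but not quitter; non responder).
2. Fix it at one visit, chosen and justified by the sponsor.
3. Test it once across the three arms at 0.05. Test the three pairs, each at 0.05, only if that test is significant. With three arms, any two pairwise null hypotheses together imply that all arms are equal, so this is a closed procedure and needs no further adjustment, provided each pairwise test holds its 5% level.
4. Make the other visits secondary, along with reduction and abstinence taken separately.
5. List AEs once, as a descriptive safety outcome.
6. State in Sample size the test, endpoint and visit to which the 133 refers.

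This keeps power 0.80 at 133 evaluable participants and w = 0.30, and needs no new data. A single binary endpoint at one visit (df = 2) would have power 0.88 at the same w. Keeping all 10 three-arm tests as primary with a Bonferroni level of 0.05 / 10 = 0.005 would cut power for each to 0.64 and require 174 evaluable participants.

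The cost is that results at the visits not chosen become secondary and cannot carry the main claim.

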#### Secondary outcomes

The secondary outcomes are to monitor AEs, quality of life, neurocognitive functioning, and spirometry, and to measure participants’ perception of and satisfaction with the product.

## Methods

### Participants

One hundred fifty-three schizophrenic regular smokers will be recruited in three centers (Smoking Cessation Centre University of Catania Medical Hospital; Psychiatric Unit of University of Catania Medical Hospital; CTA “Villa Chiara” Psychiatric Clinic) following placement of advertisements in local newspapers and radio/television network inviting them to try the e-cigarette to reduce the risk of tobacco smoking. Each participating center will include 51 eligible smokers in the study. The study protocol has been approved by the Ethical Committee of the University of Catania (Record number 674; 30-05-2013) in accordance with the Helsinki Declaration. Written informed consent will be obtained by all participants.

Inclusion criteria are: 1) schizophrenic subjects (according to DSM-IV-TR criteria) from Sicily (Italy), who smoke tobacco cigarettes, in who are in the stable phase of illness (no relapse/hospitalization and/or need to change psychopharmacological treatment in the last 12 months); 2) smoked ≥10 factory-made cigarettes/day for at least the past five years; 3) age 18 to 65 years; 4) in good general health (absence of cancer, acute myocardial infarction, unstable angina, severe cardiac arrhythmia, recent cerebrovascular incident, or severe atherosclerosis); 5) not currently attempting to quit smoking or wishing to do so in the next (a specific test will be included to check their unwillingness to quit) 6 months; 6) committed to follow the trial procedures.

Exclusion criteria are: 1) use of smokeless tobacco or nicotine replacement therapy; 2) pregnancy or breastfeeding; 3) current or recent (less than 1 year) history of alcohol and/or drug abuse; 4) other significant comorbidities according to the Investigator’s clinical assessment (for example, cancer, acute myocardial infarction, unstable angina, severe cardiac arrhythmia, recent cerebrovascular incident, or severe atherosclerosis.

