### Study design

The study is a three-arm, randomized controlled, clinical trial designed to assess the efficacy and safety of the e-cigarette with 24 mg nicotine, the e-cigarette with no nicotine, and the PAIPO nicotine-free inhalator. We adhered to Consolidated Standards of Reporting Trials (CONSORT) guidelines in the design of the trial.

At screening the diagnosis of schizophrenia will be determined using the structured clinical interview for DSM-IV axis I disorders - clinical version (SCID-I-CV); subjects with organic psychosis, learning disabilities or requiring a translator because of lack of Italian fluency will be excluded from the study. The psychopathological status of the participants will be assessed by a trained psychiatrist (blinded to the treatment conditions) using the positive and negative syndrome scale (PANSS) to evaluate the severity of illness. Written informed consent will be obtained by all eligible participants at this visit. Screening in brief is as follows: informed consent; inclusion/exclusion criteria; Case Report Form”CRF (socio-demographic factors; smoking history; SCID-I-CV; PANSS); if eligible book next appointment in 1 week.

At baseline (BL), participants will be randomized into three separate study groups. The randomization sequence will be computer generated by permuted blocks of five for each of the three study conditions (A, B, and C). Participants randomized in study group A will receive a 12-week supply of the e-cigarette with 24 mg of nicotine; those in study group B, a 12-week supply of the e-cigarette 0 mg of nicotine; participants in study group C will receive a 12-week supply of the PAIPO nicotine-free inhalator. A prospective evaluation of efficacy and safety will be repeated at an additional follow-up visit at 24 weeks. The study will consist of a total of seven visits: a screening visit, a BL visit and five follow-up visits (at weeks 4, 8, 12, 24, and 52). Three telephone contacts (TC) will be scheduled during the treatment phase (at weeks 2, 6, and 10) (Figure 3).

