### Study schedule

Participants will attend their study visits at the smoking cessation clinic at approximately the same time of day. With the exception of the BL study day, most visits will take approximately 10 to 15 minutes to complete. The BL visit will be carried out within seven days of the screening visit. At BL (study visit 1), socio-demographic factors, and detailed smoking history will be annotated and individual pack-years (pack/yrs) calculated, together with the ratings of quality of life and neurocognitive functioning assessed by the quality of life scale (QLS) and brief assessment of cognition in schizophrenia (BACS), respectively. Physical cigarette dependence and behavioral dependence will be measured with the Fagerstrom test for cigarette dependence (FTCD) and Glover-Nilsson smoking behavioral questionnaire (GN-SBQ), respectively. Additionally, levels of carbon monoxide in exhaled breath (eCO) will be measured using a portable device (Micro CO, Micro Medical Ltd, Kent, UK). Vital signs (heart rate (HR) and blood pressure (BP)), body weight, spirometry, and AEs will also be recorded at baseline.

Participants will be given a free supply of e-cigarettes or PAIPO inhalators (on average, a 4-week supply of e-cigarettes) and instructed on how to correctly use them. Key trouble-shooting support will be provided and phone numbers will be supplied for medical assistance. A full 4-week supply of nicotine or no-nicotine e-cigarettes, or PAIPO inhalators (depending on the study-arm allocation) will be also provided so that every participant will have enough disposable products for each study period; a study diary recording will be used to check for the most common AEs related to the use of e-cigarettes (for example, dry cough, mouth irritation, throat irritation, headache, shortness of breath, nausea et cetera). No emphasis on encouragement, motivation and reward for the smoking cessation effort will be provided, because this study was intended to monitor schizophrenic smokers who are unwilling to quit. Participants will be instructed to return every four weeks to obtain their 4-weekly supply of e-cigarettes or PAIPO inhalators.

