The BL (visit 1) in brief is as follows: CRF (physical examination, FTCD, GN-SBQ, QLS, BACS, HR, BP, weight, eCO, spirometry, AEs); craving/visual analog scale (VAS); MNWS; randomization into either study group A (e-cigarette 24 mg), B (e-cigarette 0 mg), or C (PAIPO); dispense 4-weeks supply of nicotine e-cigarette, no-nicotine e-cigarette or PAIPO inhalator (depending on the study-arm allocation); dispense 4-week study diary for AEs; book for next appointment in 4 weeks (week 4; study visit 2).

By and large, at week 4 (study visit 2), and week 8 (study visit 3), participants will a) receive further study diaries for the residual study periods; b) have their eCO levels and vital signs recorded; and c) return their completed study diaries and used study products. At the end of the week-12 study visit, no more products will be provided by the investigators.

Week-4 (visit 2) in brief is as follows: collect 4-week study diary for AEs; CRF (number of cigarettes/day, eCO, HR, BP); craving/VAS; MNWS; PANSS; smokers’ product preference survey; dispense next 4-week supply of nicotine e-cigarette, no-nicotine e-cigarette or PAIPO inhalator (depending on the study-arm allocation); dispense next 4-week study diary for AEs; book for next appointment in 4 weeks (week 8; study visit 3).

Week-8 and -12 (visits 3 and 4) in brief are as follows: collect 4-week study diary for AEs; CRF (number of cigarettes/day, eCO, HR, BP); craving/VAS; MNWS; PANSS; smokers’ product preference survey; dispense next 4-week supply of nicotine e-cigarette, no-nicotine e-cigarette or PAIPO inhalator (depending on the study-arm allocation); book for next appointment in 12 weeks (week24; study visit 5).

Week 24 (visit 5) in brief is as follows: collect 4-week study diary for AEs; CRF (number of cigarettes/day, eCO, HR, BP); craving/VAS; MNWS; PANSS; BACS; QLS; smokers’ product preference survey; spirometry; book for next appointment for the final visit (week 52; study visit 6).

Week 52 (visit 6) in brief is as follows: CRF (number of cigarettes/day, eCO, HR, BP); craving/VAS; MNWS; PANSS; BACS; QLS; smokers’ product preference survey; spirometry.

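### Entry sets no exhaled-CO floor, so a smoker already at or below the trial's 7 ppm abstinence limit can be randomized, and that person's later quit claims then rest on self-report alone

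*Protocol article*

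**What the plan says.** **Entry.** The Participants section requires that a candidate "smoked ≥10 factory-made cigarettes/day for at least the past five years". None of the six inclusion or four exclusion criteria mentions eCO.

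**Screening.** Under Study design, the screening record holds "socio-demographic factors; smoking history; SCID-I-CV; PANSS); if eligible book next appointment in 1 week". No eCO reading is listed there.

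**Baseline (visit 1).** Under Study schedule, "levels of carbon monoxide in exhaled breath (eCO) will be measured using a portable device". The visit summary lists "CRF (physical examination, FTCD, GN-SBQ, QLS, BACS, HR, BP, weight, eCO, spirometry, AEs" and only afterwards randomization. Table 1 also places a review of the eligibility criteria at this visit. The reading is recorded, but no entry decision depends on it.

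**Quitter.** Under Study outcome measures, abstinence means "not even a puff (together with an eCO concentration ≤7 ppm), will be calculated at each study visit". The limit is absolute.

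**Reducer.** The same section requires a self-reported fall of at least 50% in cigarettes per day, "together with an eCO levels reduction, to objectively document a reduction from baseline". This check is relative to the participant's own baseline, and no minimum fall is given.

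**The concern.** Smoking reduction and abstinence are both named under the primary objective. The eCO limit is the only objective element in the definition of abstinence. It works only if a participant who is still smoking would normally read above it, and the entry criteria do not secure that. Anyone randomized with a baseline reading at or below 7 ppm carries a biochemical condition that is met from the first day.

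False quits would be misclassification in a primary efficacy outcome. If they occur equally in all arms, they raise every quit rate and blur the contrast. If they occur more often in one arm, they bias the comparison. The second case is conceivable, because the article describes the e-cigarette and the PAIPO inhalator as physically different devices, so participants can probably tell which type they hold. Once such people are randomized, no analysis can supply the missing verification.

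**Working it through.** **Step 1: the plan's own figure.** The Sample size section gives 133 subjects from effect size 0.30, alpha 0.05 and power 0.80, then 153 after 15% drop-out. The type of effect size is not named. Read as Cohen's w in a chi-square test of 3 arms by 3 outcome classes (quitter, reducer, non-responder), with df = (3 − 1) × (3 − 1) = 4, the noncentrality is 133 × 0.30² = 11.97. Power is then 0.801, and 133 is the smallest N that reaches 0.80. Next, 133 × 1.15 = 152.95, rounded up to 153, or 51 per arm. Both figures reproduce. Neither depends on an eCO entry rule, so this point leaves them unchanged.

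**Step 2: the definitions side by side.** Take a participant who goes on smoking exactly as before, so that eCO does not change.

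| Baseline eCO | Claims abstinence | Claims a reduction of at least 50% |
|---|---|---|
| Above 7 ppm | Fails: reading still above the limit | Fails: no fall from own baseline |
| At or below 7 ppm | **Passes:** limit already met at entry | Fails: no fall from own baseline, apart from measurement variation |

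Only the abstinence check is lost at a low baseline. The reduction check survives but is weak: any fall counts, and there is little room to fall, so small fluctuations can decide the result in either direction.

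**Step 3: how many people.** The article gives no eCO distribution, so the share *s* of otherwise eligible people at or below 7 ppm is an assumption, taken from 0% to 20%. The false-claim rate *q* among them is also assumed, at 10% and 30%.

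- Affected among those randomized = 153 × *s*; per arm = 51 × *s*
- To be assessed so that 153 pass a floor = 153 / (1 − *s*), rounded up
- Points added to the quit rate = *s* × *q*, a ceiling that assumes the reading stays at or below 7 ppm at the later visit

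| *s* | Of 153 | Per arm | To assess | Added, *q* = 10% | Added, *q* = 30% |
|---|---|---|---|---|---|
| 0% | 0 | 0 | 153 | 0 | 0 |
| 2% | 3.1 | 1.0 | 157 | 0.2 | 0.6 |
| 5% | 7.7 | 2.6 | 162 | 0.5 | 1.5 |
| 10% | 15.3 | 5.1 | 170 | 1.0 | 3.0 |
| 20% | 30.6 | 10.2 | 192 | 2.0 | 6.0 |

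**Step 4: between arms.** With the same *q* in every arm, each quit rate rises by about the same amount. A bias in the difference needs *q* to differ. If it were 30% in one arm and 10% in another, the spurious difference would be *s* × 20 points: 0.4 points at *s* = 2% and 4 points at *s* = 20%. Nothing in the article says whether it would differ.

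**The case against.** The strongest reply is that the effect may be negligible. The Discussion says that smokers with schizophrenia smoke more heavily and take in more nicotine per cigarette, which argues against many low readings among people smoking at least 10 a day. A false quit also needs someone to claim total abstinence untruthfully. Participants are selected for not wanting to quit, and the Study schedule rules out encouragement or reward for cessation, so the motive is weak. Randomization should spread low-eCO entrants evenly. All of this stands, and it limits the size of the point.

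A second reply is that baseline eCO is recorded for everyone, so a sensitivity analysis can set the affected participants apart. That is true, but it identifies them without verifying their claims, and leaving them out gives up randomized participants.

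A third reply is that a condensed article may omit how smoking status is confirmed at screening. In the same vein, it does not call the entry criterion self-reported; that is inferred from the absence of any objective check. However, the article sets out numbered eligibility criteria and both outcome definitions explicitly, and the mismatch lies between those stated rules.

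Two stronger readings are tempting, and the document does not support them:

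- **That reduction claims cannot be verified either.** They need an eCO fall from the participant's own baseline, which can be tested at any starting value. The missing minimum fall is a separate matter.
- **That overstating consumption to reach 10 a day lets someone score a reduction with little or no change.** This ignores the eCO half of the reducer definition. A floor of 7 ppm would also miss most such people, and the denominator is already baseline cigarettes per day.

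**Conclusion.** The point holds for quit claims. The stated entry rules admit a person whose baseline eCO is at or below the trial's own abstinence limit, and for that person the limit gives no information. For reduction claims the check is weak at a low baseline but present.

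The size is unknown. Under the assumed 2% to 20% share and 10% to 30% false-claim rate, the quit rate is inflated by about 0.2 to 6 points; the upper end needs both assumptions at their extremes. A reader might infer a bias between arms, but that would need false claims to differ by arm, which the document neither shows nor excludes. This is a modest weakness that is cheap to close, not an error that undermines the design.

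**What to change.** Add to the inclusion criteria in the Participants section: baseline eCO above 7 ppm, read at visit 1 before randomization, with one re-test allowed within the screening window. The Study schedule puts baseline within seven days of screening, so the wording should make sure that a re-test fits in before randomization.

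The rule uses the trial's own limit and a reading already planned for that visit. The cost is one protocol line, a few true smokers screened out on a low reading, and somewhat more people to assess: about 162 to 170 for 153 randomized if the share is 5% to 10%. The sample size of 133 and 153 is unchanged. The article expects recruitment to start in September 2014, so the line can be added before the first participant enters. The reducer denominator needs no change.
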